#### Subgroup analyses

For the primary endpoint, the ANCOVA model will be extended to include an interaction between the intervention effect and (1) age (continuous variable), (2) baseline phenotypic CHD risk score (continuous variable) and (3) sex. If the p-value for interaction is <0.05, then the number and percentage of individuals with the endpoint within each randomised group, together with intervention effect (and 95 % confidence intervals) will be reported separately within categories defined by the subgroup variable. For age and baseline CHD risk score, the cut-off for the categories will be their median values at baseline.

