### Measures

Table 2 provides details of the measures collected in the INFORM study and the stage of the study at which each is assessed. The primary outcome is objectively measured physical activity, defined as average acceleration (m/s^2^) over the observation period. Participants are instructed to continuously wear the accelerometer for 7 consecutive days and nights, and to carry on with all normal activities during this time. The accelerometers are waterproof and can be worn while swimming and showering. Accelerometers have been chosen as a measure of physical activity because they cause low participant burden and are not subject to the reporting bias or recall problems associated with the self-report methods [52].

The key secondary outcome, dietary behaviour, is objectively measured by levels of six serum carotenoids (alpha-carotene, beta-carotene, lutein, lycopene, beta-cryptoxanthin, zeaxanthin). Carotenoids are biologically active pigments in plants but are not synthesised in animals and as such they represent a valid biomarker of vegetable and fruit intake [53].

Other objectively measured secondary outcomes include total, HDL and LDL cholesterol and fructosamine. We also collect self-reported secondary outcomes via an online questionnaire. They include cardiovascular risk factors (self-reported weight, smoking status, alcohol consumption, physical activity and dietary behaviour); current medication and healthcare usage; perceived risk (perception of comparative and absolute risk); cognitive evaluation of provision of CHD risk scores (understanding, accuracy, acceptability); and psychological outcomes (anxiety associated with testing, fatalism, depression, stress and mood).

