### Statistical analyses

#### Sample size calculation – randomised controlled trial

The primary outcome is between-group differences in the change (follow-up minus baseline) of the average acceleration (m/s^2^) over the observation period, measured using the Axivity AX3 3-Axis Logging Accelerometer®. The intervention will be potentially important if it increases the primary outcome by 10 %. This corresponds to an additional 10 min of brisk walking per day or an additional 3 min of jogging per day. The same effect size was used in the Understanding Risk trial by Price et al. [54] among people at high risk of CVD with one month of follow-up. This effect size is also in line with the ProActive trial that aimed to increase physical activity among individuals at high risk of type 2 diabetes [55]. To allow for four pairwise comparisons in the primary analysis, the significance level was set to 1.25 %. We calculated that 186 participants per group will be needed to detect this effect with 80 % power and 95 % confidence, assuming the estimated standard deviation (SD) of change in physical activity from baseline to follow-up is 0.05 and the correlation between physical activity at baseline and follow-up is 0.6 [56]. Allowing for an attrition rate of 20 %, we therefore aim to randomise a total of 932 participants (233 per group).

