#### Analysis design – randomised controlled trial

All trial analyses will be based on the Intention To Treat (ITT) principle. Those with missing follow-up data will be excluded from the analyses (a complete case approach). We will perform sensitivity analyses to assess the impact of missing follow-up data on the results. Participants with missing baseline data will be included in the analyses using the missing-indicator method [59].

The null hypothesis for the primary analysis is that there is no difference between any of Groups 1 to 4. Estimates of the following pairwise differences will be calculated: 1) Group 1 (control group) vs. Group 2 (lifestyle advice only) – to estimate the effect of providing lifestyle advice compared with no intervention; 2) Group 3 (phenotypic risk score and lifestyle advice) vs. Group 4 (phenotypic and genetic risk scores and lifestyle advice) – to estimate the effect of providing a genetic risk score in addition to lifestyle advice and a phenotypic risk score; 3) Group 3 + Group 4 vs. Group 1 – to estimate the effect of providing risk score information and lifestyle advice compared with no intervention, and 4) Group 3 + Group 4 vs. Group 2 – to estimate the effect of providing risk score information in addition to lifestyle advice.

Mean changes in objectively measured physical activity between baseline and 3-month follow-up will be analysed using analysis of covariance (ANCOVA). The ANCOVA model will model change (follow-up minus baseline) in objectively measured physical activity, adjusted for baseline. A test involving three degrees of freedom (3 d.f.) will be performed of the null hypothesis that there is no difference between the four randomised groups. If the p-value from this test is <0.01, this will imply that there are differences between the groups. The ANCOVA model will also be used to derive estimates of the differences in mean change and 95 % confidence intervals for each of the four pairwise comparisons described above. To avoid detracting the focus of the results from the overall 3 d.f. test, *p*-values for each of the pairwise comparisons will not be calculated.

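### The planned subgroup summary counts people with an endpoint that is continuous, and category-level results appear only if the interaction reaches p<0.05

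*Protocol article*

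**What the plan says.** The Measures section fixes the type of endpoint: "The primary outcome is objectively measured physical activity, defined as average acceleration (m/s^2^) over the observation period". The sample size section restates it as a change score: "The primary outcome is between-group differences in the change (follow-up minus baseline) of the average acceleration". The analysis section gives the model: "The ANCOVA model will model change (follow-up minus baseline) in objectively measured physical activity, adjusted for baseline".

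The Subgroup analyses section stays with this endpoint and this model: "For the primary endpoint, the ANCOVA model will be extended to include an interaction between the intervention effect and" three modifiers, listed as "1) age (continuous variable), (2) baseline phenotypic CHD risk score (continuous variable) and (3) sex". It then sets a condition, "If the p-value for interaction is <0.05", and names two outputs that follow if it is met. The first is "then the number and percentage of individuals with the endpoint within each randomised group". The second is the intervention effect with its 95% confidence interval in each category. Age and risk score are split at their baseline medians for this display. The section says nothing about category-level results when the condition is not met.

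**The concern.** There are two separate faults in one sentence.

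First, a count and percentage of people with the endpoint is a summary for a binary outcome. For a change in acceleration it has no meaning until someone chooses a cut-point, and the article contains none. An analyst must either depart from the text or invent a definition.

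Second, showing category-level effects only after a significant interaction test filters the estimates by size. An interaction that passes is likely to look larger than it is. One that fails leaves no category-level record, so readers cannot judge how consistent the effect was across age, risk and sex, and later syntheses cannot use the data. How often this would happen depends on the power of the interaction test, which the trial was not sized for.

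**Working it through.** **Does the count and percentage fit the endpoint?** Setting the sections side by side:

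- Measures: the outcome is an average acceleration in m/s², a continuous quantity.
- Sample size calculation: the quantity compared is follow-up minus baseline.
- Analysis design: the model is ANCOVA on that change.
- Subgroup analyses: the same endpoint and model, with an interaction term added.
- Categorical endpoints are dealt with separately, by logistic and multinomial regression, in the paragraph on secondary endpoints.

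No section defines a responder, so the count and percentage has no definition. The effect with its 95% confidence interval does: it is an adjusted difference in mean change. The sentence does not say which of the four planned comparisons it covers.

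**How selective is the p<0.05 condition?**

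Inputs from the sample size section: 186 evaluable per group, power 80%, significance level 1.25%, SD of change 0.05, correlation 0.6, attrition 20%. Assumptions of this check: two-sided testing (sidedness is not stated), an even split into two categories, and a normal approximation.

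1. *The plan's own figure.* 186 / 0.80 = 232.5, rounded up to 233 per group; 4 × 233 = 932. This agrees with the article.

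2. *The effect the design can detect.* The baseline mean behind the 10% increase is not given, so the 186 cannot be checked forwards. Solving backwards, difference / SD = √(2/186) × (2.498 + 0.842) = 0.1037 × 3.339 = 0.346. In m/s² this depends on how the SD is read:
   - SD 0.05 used directly: 0.0173.
   - SD 0.0447, converting the SD of change to an ANCOVA residual, 0.05/√0.8 × 0.8: 0.0155.
   - SD 0.04, that is 0.05 × √(1 − 0.6²): 0.0139.

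   The steps below use only the standardised value, so this choice does not affect them.

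3. *Precision of an interaction.* For one two-group comparison, the main contrast has standard error √(2/186) = 0.1037 SD. With an even split, each category has half the participants and the interaction is a difference of two contrasts, so its standard error is 2 × 0.1037 = 0.2074 SD.

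4. *Power.* An interaction as large as the design effect lies 0.346 / 0.2074 = 1.67 standard errors from zero. Power at two-sided 0.05 is Φ(1.67 − 1.96) = 0.386, about 39%. The chance that it is not shown by category is 1 − 0.386 = 0.614, about six in ten.

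5. *A 3 d.f. interaction test, with one group deviating.* There are 93 participants per cell, and the noncentrality is (3/4) × 0.346² / (2/93) = 4.18. Power at 0.05 is about 37%, so the picture is the same.

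6. *Size of the estimates that pass.* For a normal estimate with mean 1.67 and unit standard error, kept only when it exceeds 1.96 in absolute value, the average is about 2.66. The ratio 2.66 / 1.67 = 1.59, an overstatement of roughly 60%.

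**The case against.** The strongest defence is that only one descriptive phrase fails. The modifiers are prespecified, age and risk score stay continuous in the test, and the display cut-offs are fixed at the medians. Showing category estimates only when there is evidence of interaction is a familiar way to discourage over-reading of subgroups. The primary analysis is untouched. All of that is fair, and it limits the consequence. It does not repair the phrase. The article states the wrong summary and fixes the condition itself, so neither is a detail left to an analysis plan. The phrase might be read as the number with endpoint data, given the complete-case approach, but that is not its natural meaning. As for over-reading, labelling the results exploratory deals with it without filtering them by size.

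Some stronger readings are tempting, and the article does not support them:

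- *That the whole subgroup output is undefined.* The effect with its confidence interval is defined by the ANCOVA.
- *That a dichotomy of the primary outcome is planned.* Nothing says so; the median splits apply to age and risk score only.
- *That the interaction tests themselves would be withheld.* The condition governs the category-level results, and nothing says the tests go unreported.
- *That 0.05 contradicts the 0.01 and 0.001 under Multiplicity.* Those are thresholds for calling a 3 d.f. result convincing, whereas 0.05 here only triggers a display. Three independent tests at 0.05 would give 1 − 0.95³ = 14.3% for at least one false trigger, and less if correlated, which is likely because the risk score is built from sex-specific models that include age. Setting that figure against 1% compares different things.
- *That interactions should be believed only at p<0.01.* No section supports such a rule, and on the same approximation it would cut power to Φ(1.67 − 2.58), about 18%.

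**Conclusion.** The point holds in two parts. The count and percentage of people with the endpoint cannot be produced for a continuous change score with no responder definition. This follows from the text alone. The p<0.05 condition also makes category-level reporting selective: about 39% power for an interaction as large as the design effect, hence about six in ten such interactions not shown by category, and an average overstatement of roughly 60% among those that are.

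These figures rest on 186 evaluable per group, an even split, two-sided testing and a normal approximation. They treat age and risk score as two categories, and a continuous interaction term would have somewhat different power. An uneven split, by sex for example, would lower it. The selectivity lies in what is shown, not in the choice of subgroups. The effect on the trial's main conclusion is small, because the primary 3 d.f. test and the sample size do not depend on this sentence. It should still be corrected, since it fixes an output that cannot be delivered.

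**What to change.** Replace the sentence. For all three prespecified modifiers (age, baseline phenotypic CHD risk score, sex), and whatever the interaction p-value, report:

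- n and mean (SD) change in average acceleration for each randomised group in each category;
- adjusted differences in mean change, in m/s² with 95% confidence intervals, for the four planned comparisons in each category;
- the interaction estimate and its p-value, from the model with age and risk score kept continuous.

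Present all of this as exploratory and drop the count and percentage. No new significance threshold is needed.

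The cost is three small tables: 3 modifiers × 2 categories × 4 comparisons = 24 adjusted differences, beside 3 × 2 × 4 = 24 group means. The exploratory label matters, because some of the 24 intervals may exclude zero by chance. Recruitment is reported as complete and the trial as ongoing, so this changes analysis wording only, and is best done before the outcome data are analysed.

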#### Multiplicity

Given the number of endpoints, randomised groups and therefore comparisons, the results for the primary endpoint will be regarded as convincing if the *p*-value from the 3 d.f. test is <0.01, while the results for each secondary endpoint will be regarded as convincing if the relevant *p*-value from the 3 d.f. test is <0.001.

#### Qualitative analyses

Thematic analysis will be used to analyse the qualitative data. The transcriptions will be coded using NVivo software. To increase the rigour and validity of the analysis, and as a form of triangulation, the framework development (coding tree) will be conducted by a subgroup of three members of the team (the lead qualitative researcher and two others). In addition, a subset of 20 % of transcripts will be double-coded by two members of the research team, and disagreements will be discussed in order to reach consensus about interpretation and indexing. Analysis will involve two stages:Data management which will include: a) familiarisation with the data, including reading transcripts and notes and/or listening to the audio dialogue in order to extract main themes and ideas; b) thematic framework development, identifying the key issues and concepts present in the data and creating a coding tree which will be conducted both inductively, based on the data, and deductively, based on the research questions; c) indexing the data.Interpretation stage which will include focused or axial coding, defining the main concepts and mapping the ways in which different parts of the data are related to each other.

## Discussion

The INFORM randomised trial has been designed to contribute toward the understanding of the impact of provision of phenotypic and genetic CHD risk information on health-related behaviour change and other important clinical outcomes. Comparison between randomised trial arms will enable estimation of: 1) the effect of providing web-based lifestyle advice; 2) the effect of providing a genetic risk score in addition to lifestyle advice and a phenotypic risk score; 3) the effect of providing risk score information and lifestyle advice and 4) the effect of providing risk score information in addition to lifestyle advice. The INFORM study will also provide information on potential moderators and mediators between the intervention and health-related behaviour change and other clinical outcomes.

Even though the routine use of CVD risk scores is strongly advocated by most cardiovascular guidelines [10, 11], relatively little is reliably known about the benefits of the provision of different forms of CVD risk scores to individuals and about any potential harms (such as the possibility of increased anxiety or false reassurance). Previous systematic reviews [18, 19] have concluded that no robust recommendations can be made about the value of providing CVD risk information owing to limitations in previous studies, including lack of adequate power and lack of objective measures of health-related behaviours.

The INFORM study is well-placed to advance current knowledge on this topic because it is a trial that combines several advantages, including: a) power to identify clinically important differences between groups in this study’s principal outcomes; b) objective measures of health-related behaviours; c) simplicity of the interventions and relevance to primary care. If the intervention(s) in this trial prove to be effective, then the components of the intervention should be relatively easy to implement in primary care practice. Hence, the INFORM trial should provide a reliable evaluation of the impact of the provision of CVD risk information, thereby potentially informing policy decisions and guiding clinical practice about the routine use of CVD risk scores in primary care.

### Research governance

#### Ethical approval

Ethical approval was received from NRES Committee East of England – Cambridge Central (14/EE/1164) on 03/12/2014. NHS Research and Development assurance has been received by our lead CCG (Cambridgeshire and Peterborough CCG) and CRN: Eastern. The trial was prospectively registered at the ISRCTN Registry (ISRCTN17721237) on 12/01/ 2015. This paper details version 1.2 of the trial protocol dated 13/01/2015. The trial has been adopted by the NIHR Portfolio.

### Study sponsor

The University of Cambridge is the sponsor of this trial.

### Data handling and quality assurance

A Data Monitoring Committee is not considered appropriate for this trial considering that the likely risks to participants are known to be minimal, recruitment and follow-up are over a short period of time, and the data for this trial is both collected and stored online and, as such, is expected to have a minimal error rate. Any incidental safety information will be reported to the Trial Steering Committee (TSC). The Data Manager is responsible for the quality and integrity of data and will provide a data report to each TSC meeting. Data are stored in accordance with the University of Cambridge School of Clinical Medicine Information Governance policy which relates to sensitive/identifiable personal information collected and stored for the purposes of research.

### Patient and public involvement (PPI)

Two representatives from the PPI Panel at Cambridge University Hospitals NHS Foundation Trust were recruited in June 2014. PPI representatives have played an integral role in the INFORM study and contributed to the different stages of the research. More specifically, PPI representatives commented on the protocol, questionnaires, wording and format of the presentation of the risk score estimates, critically revised patient information sheets (both qualitative and quantitative) as well as the web-based lifestyle intervention. PPI representatives have a central role in the TSC. We expect that they will also be involved with developing newsletters and taking part in dissemination activities.

### Trial oversight

In addition to the Research Ethics Committee, the INFORM study is overseen by the TSC and Trial Management Group (TMG). The purpose of the TSC is to provide oversight of the clinical trial, with particular reference to adherence to the protocol, compliance with the Department of Health Research Governance Framework and the Guidelines for Good Clinical Practice, and the rights, safety and wellbeing of the trial participants. In addition to members of the research team, the Committee contains a number of independent members, specifically the Independent Chair, Independent Academics and PPI representatives. The purpose of the TMG is to monitor the objectives and progress of the trial, oversee day-to-day management of the study, consider any new information that may be relevant to the trial and discuss any scientific matters contained in, or relevant to, the trial. It includes investigators, the trial manager and project administrative assistant.

### Research dissemination and data preservation for sharing

The investigators will analyse data according to a predefined analysis plan in a timely manner. Members of the research team will be involved in reviewing drafts of the manuscripts, abstracts, and any other publications arising from the trial. The Chief Investigator will have final approval on all publications and press releases. Authorship of publications will be determined by ICMJE guidelines. A lay summary of the research findings will be available on the study website [29] and study participants will be notified by email when they are available.

The database manager will take responsibility for data curation and archiving, and all data sets will be kept securely with no access from unauthorised personnel. Data will be stored so that it can be accessed, used and understood by subsequent users. On completion of the data collection we will develop a data dictionary so that scientists can request release of a study dataset from the investigators. When the investigators have completed their planned analyses, the anonymised data will be made available for use by others and will be shared under appropriate data sharing agreements. Primary data and the Trial Master File will be retained securely in their original form for a minimum of 10 years.

### Trial status

Ongoing. Recruitment was completed in June 2015.

## Abbreviations

ANCOVA: analysis of covariance
BMI: body mass index
CHD: coronary heart disease
CVD: cardiovascular disease
GP: general practitioner
GRS: genetic risk score
lnGRS: natural log-transformed genetic risk score
HDL: high-density lipoprotein
ITT: Intention to Treat principle
LDL: low-density lipoprotein
NHS: the National Health Service
NHSBT: NHS Blood and Transplant
NICE: National Institute for Health and Care Excellence
PPI: Patient and public involvement
SD: standard deviation
SNP: single nucleotide polymorphism
TMG: Trial Management Group
TSC: Trial Steering Committee
3d.f: 3 degrees of freedom test
